## Abstract

**Background:**

Despite the robust body of evidence for the benefits of home-based physical exercise, there is still a paucity of data on the benefits of home-based cognitive training for older adults, especially in those at increased risk of clinical-functional vulnerability. As such, the present study aims to compare the chronic effects of a telehealth-delivered physical training intervention alone or combined with a cognitive training program in older adults at increased clinical-functional vulnerability risk.

**Methods:**

A randomized clinical trial will be conducted including 62 sedentary older individuals classified as at increased risk of clinical-functional vulnerability based on their Clinical-Functional Vulnerability Index score. Participants will be randomly allocated in a 1:1 ratio to one of two groups, an intervention group including physical training combined with cognitive training, or an active control group including physical training alone. Both groups will receive home-based supervised training remotely for 12 weeks and will be assessed for the primary and secondary outcomes of the study before and after the training period. Primary outcomes include cognitive function and dynamic balance with a dual task. Secondary outcomes encompass physical, cognitive, and occupational performance, functional capacity, quality of life, and anxiety and depression symptoms, as well as hemodynamic measures. Data analysis will be performed by intention-to-treat and per protocol using mixed linear models and Bonferroni’s post hoc (*α* = 0.05).

**Discussion:**

Our conceptual hypothesis is that both groups will show improvements in the primary and secondary outcomes. Nevertheless, we expect physical combined with cognitive training to improve cognitive function, dual task, and occupational performance to a greater degree as compared to physical training alone.

**Trial registration:**

NCT05309278. Registered on April 4, 2022.

**Supplementary Information:**

The online version contains supplementary material available at 10.1186/s13063-023-07567-8.

## Background

The aging process is a natural and multifactorial phenomenon that involves the complex interaction between biological and molecular mechanisms. This interaction may differ between individuals, but overall, reductions in autonomy and independence are observed as people age [51]. As a consequence of these losses, there is a progressive increase in older adults’ social, physical, and cognitive vulnerability [44], with a marked raise on the incidence of diseases and the risk of physical disability, dependency, and mortality in those objectively classified as being at an increased risk of clinical-functional vulnerability [20]. In this sense, the latter covers multidimensional aspects of older individuals’ health, encompassing domains related to functional capacity and mobility, and also cognition, communication, self-perceived health, among others [35].

Physical exercise is an ally for improving the health of older individuals at increased risk of clinical-functional vulnerability, which has been evidenced as a key non-pharmacological strategy towards this goal [33]. Indeed, a reduction in the physical activity levels of older adults is strongly associated with increased cardiovascular risk, social isolation, frailty, sarcopenia, cancer, diabetes, and other metabolic diseases [10]. Regular physical exercise, on the other hand, brings about several benefits in physical fitness and functional capacity, such as increases in muscle mass, strength, power, agility, balance, maximal oxygen uptake, and independence in carrying out activities of daily living [24, 26, 31, 47, 50].

Meanwhile, cognitive impairments are also responsible for the increased clinical-functional vulnerability risk in some older adults. In these individuals, exposure not only to physical exercise but also to cognitive exercises might be advantageous [4, 28, 45]. In fact, aging is linked to structural changes in some regions of the brain, such as the frontal and medial temporal lobes, which gradually impair older people’s capacity to solve new problems [58]. Cognitive training, therefore, aims at improving different cognitive functions such as memory, language, attention, and processing speed, as well as depression, possibly delaying age-related cognitive decline [18, 42]. A previous randomized controlled trial analyzed the effect of cognitive training in 2832 older individuals [42]. The authors observed improvements in aspects related to memory, reasoning, and processing speed, coupled with lower self-reported difficulty in performing instrumental activities of daily living, ultimately leading to a lower cognitive decline and greater independency levels compared to the control group.

A risk factor that can also influence the physical and cognitive capacity of older individuals is social isolation [37, 52]. Recently, the world population was forced to shelter at home as a consequence of several lockdown measures to reduce the transmission of the COVID-19 virus. Such measures, although necessary, were not without a price [2]. Several reports now indicate that lockdown measures negatively impacted individuals’ physical and cognitive well-being [8, 49], and increased loneliness [19], especially in at-risk populations such as older adults. In the latter, social isolation typically leads to an increased risk of cardiovascular and autoimmune diseases, functional impairment, and neurocognitive and mental health problems [7], as well as anxiety and depression symptoms [46]. Because the restrictions imposed by the pandemic prevented these individuals from attending commonly sought-after activities to improve their physical and cognitive well-being, such as going to a gym, for example, alternatives needed to be found.

Telehealth delivered exercise training was one such alternative [17]. Specifically, the use of remotely supervised home-based physical exercise programs delivered via telehealth as a safe strategy to deliver training interventions during the COVID-19 pandemic proved successful [15]. A recent randomized controlled trial tested the effectiveness of this approach and concluded that a synchronous telehealth-delivered exercise program improved physical fitness, quality of life, and mood in older adults [3]. As a result, home-based online training is expected to remain a viable exercise tool even after the pandemic is over [5].

Despite the current body of evidence on the benefits of home-based physical exercise, there is still a paucity of data on the benefits of home-based physical exercise combined with cognitive training for older individuals, especially those at greater risk of clinical-functional vulnerability. As such, the present study aims to investigate the effects of a telehealth-delivered physical training intervention combined with cognitive training as compared to physical training alone in older adults at increased risk of clinical-functional vulnerability. Herein, we will report the protocol of the REPHYCOVE Study. We hypothesized that combined physical and cognitive training would result in additional positive effects for the studied population, compared to physical training alone, on cognitive function, dual task, and occupational performance.

## Methods

### Trial design

The REPHYCOVE Study is a randomized, single-blind, parallel, controlled, superiority trial. Participants are randomly allocated in a 1:1 ratio to one of two groups: an intervention group including physical training in combination with cognitive training (PCT) or an active control group including physical training alone (PT). The groups receive supervised training remotely for 12 weeks and are assessed for the primary and secondary outcomes of the study before and after the training period. The present study protocol follows as closely as possible the SPIRIT Statement recommendations [27] and was previously registered in the Clinical Trials database (NCT05309278).

### Study setting

This trial is being conducted at the Physical Education School of the Universidade Federal de Pelotas (Brazil).

### Eligibility criteria

The inclusion and exclusion criteria for participants are defined as follows:

Inclusion criteria.60 years of age or older (both sexes),Mini-Mental State Examination (MMSE) score equal to or greater than 19 points,Elementary school education complete or over,Sedentary (no current or previous participation in structured exercise > 1x/week in the past 6 months),Increased risk of clinical-functional vulnerability, as determined by the Clinical-Functional Vulnerability Index-20 (CFVI-20) questionnaire (score ≥ 7),Access to a cell phone, tablet, or notebook with internet access,Resident in the city of Pelotas, Brazil.

Exclusion criteria.Individuals who have been severely affected by COVID-19,Not retired or those retired individuals who maintained continuous or sporadic work activities,Neuromuscular deficits or any medical diagnosis that prevents the individuals from performing physical exercises,Individuals with decompensated or untreated blood pressure (> 140 × 90 mmHg) and,Individuals with visual problems that prevent them from watching the training sessions on their cell phone, tablet or notebook screen.

### Sample size

The sample size calculation was performed using the GPower v. 3.1 software, adopting a significance level of *α* = 0.05 and a power of 80%. Data used in the determination of the effect size *f* for each primary outcome (cognitive capacity: *f* = 0.35; dynamic balance: *f* = 0.22; dual-task performance: *f* = 0.20) were extracted from [16, 29], resulting in a total sample size of 52 participants. To account for possible losses during the study procedures, ten additional participants (i.e., ~ 20%) are to be recruited for the study, totaling 62 participants randomized between the two groups.

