### Randomization, assignment of interventions, and blinding

Participants included in the study are first stratified based on their MMSE score and then randomized in a 1:1 ratio between the two groups using blocks of different sizes. Randomization is performed on the www.randomization.com website by an investigator ([name]) not involved with the assessments and training of the participants after the baseline measurements are completed. The same investigator is responsible for contacting each participant by telephone to inform which group he/she is allocated to and provide detailed information on the days and time that the online training sessions will occur. Blinding is applied to the primary and secondary outcome assessors at baseline, and a similar procedure will also be applied at the post-intervention assessment procedures. Due to the nature of the interventions, the team conducting the exercise sessions and the participants performing them cannot be blinded.

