### Outcomes

Primary and secondary outcomes are assessed on three separate days, first at baseline (week 0) and then after the training intervention (week 13). Outcomes are assessed for all randomized participants, irrespective of attendance or completion status. Those who withdraw from the study at any time after randomization are also invited to perform the final study evaluations for inclusion in the intention-to-treat analysis.

The first testing day is held online. Participants answer an anamnesis, and the MMSE and IVCF questionnaires are applied. The second testing day also occurs online. During this session questionnaires related to the self-perceived quality of life, anxiety and depressive symptoms, occupational performance, working memory, and cognitive performance are applied individually by the investigators. Due to the personal nature of the data, assistance to complete the questionnaires is only provided by the investigators if completely necessary. On the third day, participants attend an in-person testing session at the Neuromuscular Assessment Laboratory of the Federal University of Pelotas. Dynamic balance, lower limb strength and endurance, handgrip strength, gait speed, and office blood pressure measures are performed. For all testing sessions, participants are instructed not to perform any intense physical activity 72 h before. Further, post-intervention measures are performed 72 h after the last training session. The temporal description of the study procedures is shown in Table 4.

**Table 4 Tab4:** Temporal description of the study protocol

		**Baseline**		**Intervention**	**Post-intervention**	
**Timepoint**	Week − 1	Week 0 (remotely)	Week 0 (in-person)	Weeks 1–12 (remotely)	Week 13 (remotely)	Week 13 (in-person)

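### The ten added participants are about 20% of the required 52 but only 16% of the 62 randomised, so 62 keeps 52 only for losses up to 16%

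*Protocol article*

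**What the plan says.** All the figures stand in the Sample size section of the protocol article. The calculation takes a significance level and power of "0.05 and a power of 80"%, and uses one effect size f per outcome. The smallest of the three is "dual-task performance: *f* = 0.20"; the others are 0.35 for cognitive capacity and 0.22 for dynamic balance. The outcome is stated as "resulting in a total sample size of 52 participants".

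The allowance for losses follows: "To account for possible losses during the study procedures, ten additional participants", described as about 20%, are to be recruited, "totaling 62 participants randomized between the two groups". No other loss percentage is given.

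Three further sections bear on the point:

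- Randomization, assignment of interventions, and blinding: participants are "randomized in a 1:1 ratio between the two groups using blocks of different sizes", after the baseline measurements are complete.
- Outcomes: assessments take place "first at baseline (week 0) and then after the training intervention (week 13"), and people who withdraw are still invited to the final assessment.
- Statistical analysis: mixed linear models with baseline values as covariates, and multiple imputation for missing data in the intention-to-treat analysis.

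**The concern.** An allowance for losses is useful only if it says what share of the randomised participants can be lost before the required number is breached. Here the percentage has the required number, 52, as its base. The losses it is meant to cover happen among the 62. The two bases give different tolerances, and the printed figure is the more favourable one.

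A reader of the section, or the team watching retention, would naturally conclude that the trial can lose about one participant in five and still hold the number on which its power statement rests. On the plan's own figures it cannot.

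**Working it through.** **Inputs from the Sample size section.** Required number 52; added 10; randomised 62; allowance about 20%; alpha 0.05; power 80%; smallest f = 0.20. From the other sections: two equal groups and two measurement times.

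**Input not in the document.** The correlation between baseline and post-intervention values, here called rho. It is assumed to be 0.5, with a range shown.

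**1. Reproducing 52.** Take the group-by-time interaction F test in a repeated-measures design with m = 2 times. The noncentrality is lambda = N × f² × m / (1 − rho), with 1 and N − 2 degrees of freedom. With f = 0.20 and rho = 0.5, N = 52 gives lambda = 52 × 0.04 × 2 / 0.5 = 8.32 and power 0.807. It is the smallest even total that reaches 0.80. With rho = 0.4 the required total would be 62, and with rho = 0.6 it would be 42. So 0.5 is a plausible planning value because it returns 52, but the article does not state it.

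**2. Reproducing 62.** 52 + 10 = 62, and 52 × 1.2 = 62.4. The stated total agrees with a mark-up of about 20% on 52. It does not agree with 52 / (1 − 0.20) = 65.

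**3. What 62 tolerates.**

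- As a share of the required number: 10/52 = 19.2%.
- As a share of those randomised: 10/62 = 16.1%.
- At 16% loss: 62 × 0.84 = 52.1 remain.
- At 17% loss: 62 × 0.83 = 51.5 remain.
- At 19.2% loss: 62 × (1 − 10/52) = 50.1 remain.
- At 20% loss: 62 × 0.80 = 49.6 remain, that is 49 or 50.
- To keep 52 at 20% loss: 52 / 0.80 = 65, or 66 for equal arms. That is 3 or 4 more than 62.

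None of step 3 depends on rho.

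**4. Power, conditional on assumptions (f = 0.20, rho = 0.5).** For the adjusted column, conditioning on baseline reduces the variance of the comparison from 2(1 − rho) = 1.0 to 1 − rho² = 0.75, in units of the outcome variance. Lambda is therefore multiplied by 4/3, with N − 3 denominator degrees of freedom.

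| Participants with outcome | Unadjusted interaction | Baseline-adjusted comparison |
|---|---|---|
| 52 | 0.807 | 0.904 |
| 50 | 0.791 | 0.892 |
| 49 | 0.783 | 0.886 |

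With rho = 0.3, the baseline-adjusted power at 49 is 0.819.

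**The case against.** **The percentage describes the ten added people.** Read literally, it is attached to the ten participants, and ten is 19.2% of 52. On that reading the sentence is correct, and the article nowhere predicts that 20% of those randomised will be lost. This stands as a matter of grammar. But it is the only loss-related percentage in the section, and the purpose given for the ten is to cover losses. Readers will take it as the tolerated loss, which it is not. If only a mark-up was meant, the sentence still leaves the real tolerance unstated.

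**Losses are mitigated elsewhere.** All randomised participants are to be assessed whatever their attendance, and the intention-to-treat analysis imputes missing outcomes. It is true that leaving the training is not the same as losing the outcome. Imputation, however, does not bring back the information in an outcome that was never measured, and the plan itself adds participants because losses cost something.

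**The power consequence is not established.** This is the strongest point, and it stands. A reader might infer that the trial falls below 80% power at a 20% loss, or that 52 has no slack. The document does not support either as fact. Both rest on a correlation that it does not give and on an unadjusted interaction test, whereas the Statistical analysis section plans models with baseline values as covariates. If that amounts to a baseline-adjusted comparison, power at 49–50 stays near 0.89 under the same inputs.

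**Conclusion.** The point holds as one of head-count. On the article's own numbers, 62 randomised preserves the required 52 for losses up to about 16% (10 of 62), not 20%. At a 20% loss the trial is two or three participants short of 52. This conclusion needs no assumption beyond reading losses as a share of those randomised.

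The consequence is small. Under an assumed correlation of 0.5 and an unadjusted test, the cost at 20% loss is 1.6 to 2.4 percentage points of power for the smallest stated effect (80.7% falling to 79.1% or 78.3%). It should not be reported as a demonstrated loss of the planned power. The matter is one of correct statement and does not put the design or the analysis in question.

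**What to change.** Restate the sentence in the Sample size section along these lines: 62 randomised participants allow for up to about 16% loss (10 of 62) while keeping the required 52.

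If a power figure at 20% loss is added (about 78–79% for f = 0.20, against 80.7% at 52), label it as conditional on a correlation of 0.5 and an unadjusted two-by-two interaction test, and note that the planned baseline-adjusted model may have higher power.

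The cost is one sentence and a slightly less favourable stated tolerance. No extra enrolment and no change to the analysis are needed. The team also gains a correct retention limit to watch: no more than ten participants without a final outcome.

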### Recruitment

The recruitment period began in July 2022 and is still ongoing. Participants are recruited voluntarily through notes published in local or regional newspapers, invitations posted on social media, and advertisements posted at several Basic Health Units in the city of Pelotas, Brazil. Those individuals who respond to our advertisement are contacted by two study team members ([name] and [name]). They are asked key questions related to age, working activities, and whether the person had internet access as an initial filter before directing the individual to the second phase of recruitment. Whenever the previous criteria are fulfilled, the investigators apply an anamnesis, the MMSE and the CFVI-20 questionnaires online through the Google Meet platform to verify if the participant meet the remainder of the inclusion criteria (see above). Those deemed eligible are invited to read and sign an online informed consent form on the Google Forms® platform containing detailed information about the study, which is followed by the schedule of a baseline measurements session (herein defined as weeks − 1 and 0).

### Randomization, assignment of interventions, and blinding

Participants included in the study are first stratified based on their MMSE score and then randomized in a 1:1 ratio between the two groups using blocks of different sizes. Randomization is performed on the www.randomization.com website by an investigator ([name]) not involved with the assessments and training of the participants after the baseline measurements are completed. The same investigator is responsible for contacting each participant by telephone to inform which group he/she is allocated to and provide detailed information on the days and time that the online training sessions will occur. Blinding is applied to the primary and secondary outcome assessors at baseline, and a similar procedure will also be applied at the post-intervention assessment procedures. Due to the nature of the interventions, the team conducting the exercise sessions and the participants performing them cannot be blinded.

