### Primary outcomes measures

The primary outcomes of this study will focus on changes in cognitive function (as assessed by the MSSE score) and dual-task performance (measured during the TUG test) from baseline to post-intervention. This selection is motivated by the increased fall risk observed in older adults during concurrent tasks, such as walking while engaging in other cognitive or motor activities. Considering that daily life entails a wide range of dual- and multi-tasks, interventions that positively impact cognitive and functional outcomes are imperative for older individuals at a heightened risk of clinical-functional vulnerability [12].

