### Statistical analysis

Analyses will be performed using the SPSS software v. 25.0, adopting an *α* = 0.05. Descriptive data will be presented as means, standard deviations, 95% confidence intervals, or absolute and relative frequencies. Data normality will be tested by the Shapiro–Wilk test, and the Levene test will test the homogeneity of variances. Primary and secondary outcome analyses will be conducted using mixed linear models with “treatment group x timepoint” interaction terms and using baseline values as covariates. An intention-to-treat analysis will include all randomized participants, in which missing data will be imputed using multiple imputations. In contrast, a per-protocol analysis will be performed with only those participants with an attendance rate  ≥ 80%. Effect sizes between-group will be computed based on Cohen’s *d* and the 95% confidence interval.

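### MMSE stratifies the randomisation but is not named in the analysis model for dual-task or any secondary outcome, a small and conditional loss of precision

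*Protocol article*

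**What the plan says.** The section on randomisation and blinding in the protocol article says "Participants included in the study are first stratified based on their MMSE score and then randomized in a 1:1 ratio between the two groups". The block sizes vary. The section gives no cut-points and no number of strata.

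The Statistical analysis section sets one model for every primary and secondary outcome: a mixed linear model with a group-by-timepoint interaction, "interaction terms and using baseline values as covariates". It names neither MMSE nor the stratification factor. The intention-to-treat analysis takes in all randomised participants, with multiple imputation.

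The two primary outcomes are the MMSE score and dual-task performance during the TUG test. The Sample size section bases its figure on three effect sizes, the smallest being "dual-task performance: *f* = 0.20". It reports "resulting in a total sample size of 52 participants" and, after an allowance for losses, "totaling 62 participants randomized between the two groups".

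**The concern.** Stratified blocks keep the arms balanced on MMSE category. If that category predicts the outcome and the model leaves it out, variation that the design has removed from the group comparison stays in the residual. The model then reports a standard error above the true one, and the test rejects less often than its nominal 5%.

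The MMSE outcome is covered because its own baseline is the stratifier. Dual-task performance is the outcome to watch. It is co-primary, it has the smallest planned effect, and the article presents it as a probe of cognitive capacity, with animal naming during the walk. Entry MMSE can range from 19 to 30, so there is spread to adjust for. Verbal fluency and digit span are also cognitive measures. What is at stake is some precision, in a trial planned with almost no spare power.

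**Working it through.** **The plan's own figure.** For a repeated-measures ANOVA within-between interaction with 2 groups, m = 2 timepoints, α = 0.05 and an assumed pre-post correlation ρ = 0.5 (not stated in the article):

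λ = f²·N·m/(1−ρ) = 0.04 × 52 × 2 / 0.5 = 8.32, on 1 and 50 degrees of freedom, gives power 0.807.

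So f = 0.20 reproduces N = 52. The other two effect sizes need fewer participants (f = 0.22 gives 44; f = 0.35 gives 20). Nothing below changes this.

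**Inputs for the check.** From the article: stratification on MMSE, 1:1 allocation, varying blocks, N = 52 evaluable and 62 randomised. Assumed, because the article does not give them:
- two MMSE strata split at the median of a roughly normal score
- blocks of 2 and 4
- pre-post correlation 0.6 for the outcome
- partial correlation r of continuous MMSE with the week-13 outcome, given that outcome's baseline, varied from 0 to 0.5
- the model read as an ANCOVA on the single post-baseline value

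**Analytic result.** A median split of a normal score keeps a share 2/π ≈ 0.64 of r². With exact balance on the stratum, omitting it inflates the standard error by 1/√(1 − (2/π)r²):
- r = 0.2: 1/√(1 − 0.0255) = 1.013
- r = 0.3: 1/√(1 − 0.0573) = 1.030
- r = 0.4: 1/√(1 − 0.1019) = 1.055

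**Simulation**, 4,000 trials per setting. Monte Carlo error is about 0.0035 on type I error and about 1% on the ratio of model to empirical SE. The first four result columns are at N = 62 under no effect. The last is at N = 52 with a standardised difference of 0.63, chosen to give about 80% power.

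| r | Model SE, stratum out / in | Model SE / empirical SE, stratum out | Type I, out | Type I, in | Power, out → in |
|---|---|---|---|---|---|
| 0 | 0.2037/0.2039 = 0.999 | 0.999 | 0.053 | 0.052 | 0.783 → 0.782 |
| 0.2 | 0.2040/0.2017 = 1.011 | 1.012 | 0.047 | 0.050 | 0.797 → 0.802 |
| 0.3 | 0.2042/0.1987 = 1.028 | 1.023 | 0.045 | 0.051 | 0.794 → 0.810 |
| 0.4 | 0.2039/0.1935 = 1.054 | 1.033 | 0.038 | 0.050 | 0.795 → 0.826 |
| 0.5 | 0.2039/0.1875 = 1.087 | 1.082 | 0.034 | 0.048 | 0.798 → 0.847 |

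The ratio of the two model standard errors follows the analytic values closely. The ratio to the empirical SE is noisier. At N = 52 under no effect it is 0.981, 1.014 and 1.046 at r = 0.2, 0.3 and 0.4, with type I error 0.057, 0.046 and 0.045. At N = 62 the type I errors at 0.2 and 0.3 cannot be told apart from 0.05. The value at 0.4 can: (0.05 − 0.0375)/0.0035 ≈ 3.6 Monte Carlo errors.

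**Continuous MMSE instead of the stratum.** The standard error without it is larger by 1/√(1 − r²) = 1.021, 1.048 and 1.091 at r = 0.2, 0.3 and 0.4. Simulated power with it in the model at N = 52 is 0.806, 0.821 and 0.850.

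**The case against.** The strongest reply is that the omission is inferred. The article does not say that only each outcome's own baseline is used, and MMSE is itself a baseline value, so the wording does not strictly exclude it from the other models. A full covariate list is also often left to an analysis plan, and none is shown here. The ambiguity stands, and the point should not be put as proof that MMSE is excluded. But the article does state a covariate set for all outcomes, and that set does not name the factor on which the design stratifies. The same sentence settles the matter under either reading.

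Three stronger readings are tempting and are not supported.

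- A reader might infer that the confidence intervals are too wide for every outcome other than MMSE. That needs MMSE to predict the outcome beyond its own baseline. This is plausible for dual-task, verbal fluency and digit span, and probably negligible for handgrip or blood pressure. At r = 0 nothing is lost.
- A reader might apply 1/√(1 − r²) and conclude that the intervals are 2%, 5% and 9% too wide, with type I error near 0.033 at r = 0.4. That formula assumes exact balance on the continuous score. Stratified blocks balance categories. The larger figures are the precision available from adding a continuous prognostic covariate; they do not measure the conservatism caused by ignoring the strata.
- A reader might say that the benefit of stratifying is thrown away, or that the result is invalid. The balance between arms remains whatever the model, the estimate is unbiased, type I error is not inflated, and N = 52 stands.

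**Conclusion.** The point holds as a minor one of efficiency and consistency. On the natural reading of the Statistical analysis section, the stratification factor is missing from the models for dual-task and the secondary outcomes. Where MMSE is prognostic beyond the outcome's own baseline, the reported standard error is slightly too large and the test slightly conservative.

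For partial correlations from 0.2 to 0.4 with two strata, the excess is about 1% to 3% in simulation at N = 62, or 1.3% to 5.5% analytically. Type I error is about 0.047 to 0.038. The power gained by adding the stratum at N = 52 runs from about half a point at 0.2 to 2 points at 0.3 and 3 points at 0.4.

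These sizes rest on the assumed correlations, a median split and an ANCOVA reading of the model, none of which the article states. Severity is low.

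**What to change.** Add to the Statistical analysis section: *All models include the MMSE randomisation stratum (or continuous baseline MMSE) as a covariate; for the MMSE outcome, its own baseline serves this purpose.* The choice between stratum and continuous score should be fixed before any comparison by group. The continuous score gains somewhat more if the relation is roughly linear.

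The covariate should act on the week-13 response. If baseline values were also kept as responses in a two-timepoint random-intercept model, a stratum main effect alone would leave the group-by-timepoint contrast unchanged.

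The cost is about one degree of freedom per model with a two-level stratum or a linear term. MMSE is already collected at screening and baseline, so no new data are needed and the sample size does not change.
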